#### Brain imaging covariates

2.4.4

Cerebral spinal fluid and motion‐related signals removed via regression (Behzadi, Restom, Liau, & Liu, 2007; Chai, Castañán, Öngür, & Whitfield‐Gabrieli, 2012), then will be low‐pass filtered at 0.1 Hz to retain the low frequencies relevant for connectivity estimation. ROI analysis will be the same as described above for thermal stimulation fMRI. Resting‐state ASL will be used as a covariate in fMRI analyses to account for baseline differences in CBF. We will use pseudocontinuous ASL (pCASL; spatial resolution = 3.44 × 3 × 44 × 7 mm^3^; TR/TI = 4000/1650 ms; slices = 17) using body coil RF transmission and 32‐channel SENSE head coil reception and inflowing blood water will be magnetically labeled using a long (1,650 ms) string of short (0.5 ms) Hanning pulses and then analyzed (Wang et al., 2002).

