### Sample/participants

2.3

Subjects will be recruited using emails, letters and flyers circulated in a southeastern university, its academic medical center and the surrounding metropolitan area. Email communications will be managed by institutional mass‐email distribution services and will prioritize prospective participants who have expressed an interest in participating to either a participating physician or a recruitment platform such as ResearchMatch, a national health volunteer registry that was created by several academic institutions and supported by the U.S. National Institutes of Health as part of the Clinical Translational Science Award (CTSA) program. Recruitment letters will be mailed to prospective participants who have either expressed interest in the study to their physician or were identified as candidates through chart review. Flyers will be posted throughout the medical center and will adhere to IRB guidelines outlining transparency and undue coercion; furthermore, these flyers will also be posted throughout the surrounding area at community centers and assisted living facilities. Because we are interested in the continuous measure of age, we will enroll 60 subjects to yield a final continuous sex‐balanced stratified sample of adults aged 30–89. We will stratify by age range (to allot 5 males/5 females) to each of six age strata: 30–39, 40–49, 50–59, 60–69, 70–79, 80–89. We will identify females who are pre‐ and post‐menopausal to control for hormone status on psychophysical and neurophysiological pain.

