Next, functional images will be aligned to each other within runs using rigid‐body coregistration in SPM 12 (Penny, Friston, Ashburner, Kiebel, & Nichols, 2007). Images will be coregistered to the T1‐weighted structural image and the transformation of the structural image to MNI space will be applied to the functional images, followed by resampling, yielding functional images at 3mm isotropic resolution. We will spatially smooth with a 6mm‐FWHM Gaussian kernel.

We will use region of interest (ROI) masks from the WFU PickAtlas tool box to delineate the anatomical boundaries for ROIs in our a priori hypotheses (Maldjian, Laurienti, & Burdette, 2004; Maldjian, Laurienti, Kraft, & Burdette, 2003). For sensory regions/lateral pathway, these are: anterior cingulate cortex, primary somatosensory cortex and secondary somatosensory cortex. For affective regions/medial pathway, these are: amygdala, periaqueductal gray, hypothalamus, pre‐frontal cortex, insula, and hippocampus.

Standard SPM12 approaches will be used to generate first‐level T‐maps. We will model activation as the contrast of a target temperature relative to baseline or relative to warmth (including ramp up and ramp down periods as covariates of no interest in the generalized linear model). These first‐level maps containing activation changes due to the temperature contrasts (mild pain > warmth, moderate pain > warmth, and moderate pain > mild pain) will be exported from SPM for hypothesis testing (Table 1).

**TABLE 1 jan14514-tbl-0001:** Index of protocol‐relevant acronyms and their meaning

3T	3 Tesla
ASL	Arterial spin labeling
BOLD	Blood oxygenation level dependent
BPISF	Brief pain inventory‐short form
CBF	Cerebral blood flow
EPI	Echo planar imaging
fMRI	Functional magnetic resonance imaging
FOV	Field of view
FWHM	Full width half maximum
HAMD	Hamilton depression scale
IRB	Institutional review board
JNP	Just noticeable pain
*M*	Mean
MNI	Montreal neurological institute
MP	Moderate pain
MRI	Magnetic resonance imaging
pCASL	pseudo‐continuous arterial spin labeling
RF	Radio frequency
ROI	Region of interest
*SD*	Standard deviation
SENSE	Sensitivity encoding
SES	Socioeconomic status
SPM 12	Statistical parametric mapping version 12
SPSS	Statistical package for social sciences
STAI	State trait anxiety inventory
STROBE	Strengthening the reporting of observational Studies in epidemiology
TE	Echo time
TFE	Turbo field echo
TR	Repetition time
WFU	Wake forest university
WP	Weak pain

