Age and sex associations with functional connectivity will be tested using the connectivity (Z) matrices for the relevant ROI for sensory and affective pain regions using the median connectivity value within the network for each subject. Linear regression analyses will be used to assess the age group effect on the overall connectivity values after co‐varying (adjusting) for regional gray matter volume and resting cerebral blood flow (CBF) as measured by pCASL generation software described below. As with the activation analyses, more specific age (years) and sex associations with activation will be assessed within each of the age groups. We will also examine the association of psychophysical data with regional brain connectivity metrics. To correct for multiple comparisons in brain imaging data we will use 3dClustSim (Cox, 1996; Cox & Hyde, 1997; Gold et al., 1998).To calculate the corrected *p* value of the brain signal in a respective ROI. This program uses the intrinsic volume and Monte Carlo simulations set at 10,000 iterations. A corrected voxel size of activation will be provided for each ROI to determine statistical significance. Data distributions will be evaluated and transformed as needed to meet the assumptions of the specific statistical methods and p‐values of 0.05 will be used for all tests.

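### The connectivity group model adjusts for gray matter and blood flow but not for residual head motion, so the age test in this secondary analysis may exceed its 5% error rate

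*Protocol article*

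**What the plan says.** All references are to the Protocol article.

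- **Realignment** (Neurophysiological testing): "functional images will be aligned to each other within runs using" rigid-body methods in SPM12. This step yields movement parameters for each person.
- **Nuisance removal and filter** (Brain imaging covariates): CSF and motion-related "signals removed via regression" come first. The data are then low-pass "filtered at 0.1 Hz to retain the low frequencies relevant for connectivity estimation". No high-pass edge or trend term is named.
- **Outcome** (Data analysis, Aim 2): age and sex associations are tested "using the median connectivity value within the network for each subject".
- **Group covariates** (same section): the age effect is adjusted "for regional gray matter volume and resting cerebral blood flow (CBF) as measured by pCASL". Head motion is not among them.
- **Error rate** (same section): "0.05 will be used for all tests".
- **Size and status**: "we will enroll 60 subjects to yield a final continuous" sample (Sample/participants). The Abstract places resting-state connectivity among the secondary analyses of a preliminary, exploratory study.

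**The concern.** Age is the exposure, and the sample runs from 30 to 89. The article already treats gray matter volume and blood flow as age-linked confounders of the imaging outcomes. Head motion is another plausible one, and it is missing from the listed covariates.

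Removing motion signals within each person's time series is not the same as adjusting for how much people differ in movement. Where the within-person regression is imperfect, people who move more can still have systematically different connectivity. The outcome is a network median. It resists one bad region pair, but not an artefact that shifts many pairs together. If residual motion also rises or falls with age, part of an apparent age effect on connectivity would be a motion effect.

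The filter raises a lesser question. A 0.1 Hz low-pass filter keeps everything from 0 to 0.1 Hz, so the filter itself does not take out slow drift.

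**Working it through.** The article states no figure on this point, so there is nothing to reproduce. Two checks follow. Their correlations and drift sizes are assumed.

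**1. Residual motion and the age test**

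Inputs: n = 60 (Sample/participants) and alpha 0.05 (Data analysis, Aim 2), taken as two-sided because the article does not say. There is no true age effect. Let r1 be the age–motion correlation, and r2 the motion–connectivity correlation that remains after the planned within-person regression. Age is treated as continuous.

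Without a motion covariate, the spurious age–connectivity correlation is r = r1 × r2. The noncentrality of the t test is r√n / √(1 − r²).

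- r1 = r2 = 0.2: r = 0.04; noncentrality = 0.04 × 7.746 / √(1 − 0.0016) = 0.31.
- r1 = 0.2, r2 = 0.4: r = 0.08; noncentrality = 0.62.
- r1 = r2 = 0.4: r = 0.16; noncentrality = 0.16 × 7.746 / √(1 − 0.0256) = 1.26.

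| r1 / r2 | Rejection, noncentral t | Rejection, simulation | Simulation with motion covariate |
|---|---|---|---|
| either = 0 | 5% | about 5% | about 5% |
| 0.2 / 0.2 | 6.1% | 6.1% | 4.9% |
| 0.2 / 0.4 | 9.4% | 9.3% | 5.1% |
| 0.4 / 0.4 | 23% | 23% | 5.0% |

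The simulation used 20,000 data sets per setting. Using 56 instead of 58 degrees of freedom, to allow for sex and the age-by-sex term, leaves the noncentral t results unchanged at this precision.

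**2. Drift under a low-pass filter**

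Take two unrelated region signals of unit variance that share a linear drift of a signal SDs. If nothing removes the drift, the spurious correlation is a² / (1 + a²).

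- a = 0.5: 0.25 / 1.25 = 0.20.
- a = 1: 1 / 2 = 0.50.
- a = 2: 4 / 5 = 0.80.

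Simulation at an assumed TR of 2 s and run length of 300 or 480 s gives 0.19–0.20, 0.50 and 0.80 after low-pass filtering alone. (The article gives a 2 s TR for the task runs only.) Adding linear detrending gives about 0.00. A band-pass of 0.008–0.1 Hz without detrending leaves 0.04–0.06, 0.15–0.19 and 0.41–0.49, so trend terms are the safer remedy.

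These values leave out the planned CSF regression. I added it for 240 volumes, with drift at 10%, 20% or 30% of variance and a CSF regressor averaged over 50 noisy voxels (all assumed). Without the CSF step the spurious correlation is about 0.10, 0.20 and 0.29. With it:

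- CSF carries all or half of the drift variance: at most about 0.02.
- CSF carries a quarter of it: about 0.03.
- CSF carries none of it: no reduction.

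**The case against.** A reader might infer that age-linked movement simply stays in the connectivity outcome. The article does not support that. It regresses out motion signals before filtering and realigns images within runs, so only a residual can remain. The size of that residual is unknown, and the error rate returns to 5% if it is unrelated to either age or connectivity. This limits the size of the point. It does not remove it, because the listed group covariates contain nothing that would catch a residual.

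A reader might also infer that drift will be read as an age effect. That does not follow. Drift of similar size in everyone shifts the general level of connectivity, not its slope on age, and nothing in the article says that drift varies with age. If CSF shares the drift, the planned CSF regression also removes most of it. Moreover, an article can leave a high-pass cut-off or detrending step to the fuller plan. The drift part is therefore a request to confirm and state the step.

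The same argument from condensation can be made for the motion covariate. It is weaker there, because the article does list the adjustment variables for this regression, and the fix changes a stated model.

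Finally, the Data analysis section makes the age-by-sex interaction the effect of main interest. Motion biases that term only if its relation to age or to connectivity differs by sex. The percentages above concern the age effect and should not be carried over to the interaction.

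**Conclusion.** The point holds in limited form and is minor. In a secondary analysis where age is the exposure, residual head motion is a plausible confounder that the stated group model does not adjust for. The cost to the age test ranges from nothing (either correlation zero) to a false-positive rate of about 23% (both 0.4), with 6% at 0.2 and 0.2. The range rests on assumed correlations, a two-sided 5% test and n = 60. It shows what could happen, not what the study will show.

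Drift is secondary. Whatever survives CSF regression would add error to the connectivity values, and no age bias from it can be claimed. The hypotheses on thresholds, unpleasantness and task activation do not depend on this model or this filter.

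**What to change.** 1. **Data analysis, Aim 2:** add each person's mean framewise displacement in the resting run, computed from the realignment parameters, to the group models for connectivity. Report the age and sex results with and without it, and report its association with age and sex.
2. **Brain imaging covariates:** put linear trend terms (or a high-pass edge of about 0.01 Hz) in the same regression as the CSF and motion signals, or state that the fuller plan already does so. Trend terms are preferable, since a band-pass alone left some linear drift in the check above.

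The cost is a change of wording, a re-run of the analysis script and one degree of freedom per model; no new data are needed. The one drawback is that if movement and true connectivity share an age-related cause, the adjusted age effect may be somewhat conservative. Hence the request to show both models.

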### Ethical considerations

2.5

The Vanderbilt University Institutional Review Board (IRB) and ethics committee approved the study protocol. All activities included in this research protocol meet criteria for minimal risk interventions as defined by U.S. Federal Regulations and as approved by the university IRB. This research does not include vulnerable populations, as all subjects are adult volunteers with normal mental status.

Subjects will be carefully screened for psychological or medical contraindications to the proposed research methods. We will adhere to international standards and local requirements for MRI safety screening. The magnetic resonance procedure itself does not use ionizing radiation and there are no common physical risks to MRI scanning if proper procedures are followed. Some subjects develop anxiety in the MRI scanner due to the enclosed space. We will specifically and carefully inform subjects that they may end the MRI portion of the study at any time for any reason without penalty. If subjects suffer an anxiety reaction, study staff and physicians will ensure the participant is calm and safe prior to exiting the scanner area. The Medoc PATHWAYS system has built in safeguards against overheating and does not reach temperatures that could produce tissue injury. Subjects can remove the probe within seconds, as the probe is held in place by easy to grip Velcro strips and can stop the scan at any point. All spontaneous reports of adverse events by subjects, observations by clinical research staff and reports to research staff by family or healthcare providers will be investigated and reported to the university IRB as is appropriate.

Subjects will be provided with a written informed consent approved by our IRB. This consent will be reviewed in a private setting and all questions will be answered by research staff prior to obtaining participant signature. We will make every attempt to ensure that subjects are comfortable and respected. We will address any questions regarding their concerns and offer referrals to counseling or other mental health services if our screening procedures suggest such referrals are warranted. Subjects will be provided with a copy of their signed consent. A copy of the signed consent will be maintained in a secure, locked, confidential research file.

### Data analysis

2.6

Statistical approaches for the analysis of the psychophysical and neurophysiological data will mirror each other. Age (continuous) and sex (male, female), and a term specifying the interaction of age and sex will be entered into general linear modeling modules in SPSS (psychophysical) and SPM (neurophysiological). We are hypothesizing different patterns of association of age with psycho‐ and neurophysiological data for males and females therefore the interaction term will be the primary effect of interest in these analyses. Main effects of ageing and sex will be tested; however, they will serve as covariates in the primary analyses. All data distributions will be evaluated and transformed as needed to meet the assumptions of the specific statistical methods. All statistical significance tests will maintain Type I error rates (alpha values) of no more than 0.05.

#### Aim 1

2.6.1

The temperature at which JNP, WP, and MP is perceived (Aim 1, Hypothesis 1), and the subject's respective affective rating of the pain (Aim 1, Hypothesis 2) at each sensory level, comprise the key dependent variables for Aim 1. Descriptive and graphical summaries of the temperatures (intensities) and affective (unpleasantness) ratings will be generated at each of the three self‐reported sensory thresholds (JNP, WP, and MP), and for each of the stratified levels of age, to inform linear and possible nonlinear associations of age with the intensity and unpleasantness sensations. Linear mixed effects analysis incorporating robust variance estimation (i.e., generalized estimating equations) will be used to test the hypotheses that for a given self‐reported sensory threshold, temperatures are higher, and ratings of unpleasantness are lower with increasing age. This effect would be indicated by a statistically significant interaction of age level with self‐reported sensory level on the dependent variables (Aim 1, Hypothesis 1: temperature; Aim 1, Hypothesis 2: unpleasantness rating). A statistically significant linear or nonlinear association of age with those variables but no interaction effect will indicate an age effect on temperature and unpleasantness regardless of perceived pain.

#### Aim 2

2.6.2

Age and sex associations with functional connectivity will be tested using the connectivity (Z) matrices for the relevant ROI for sensory and affective pain regions using the median connectivity value within the network for each subject. Linear regression analyses will be used to assess the age group effect on the overall connectivity values after co‐varying (adjusting) for regional gray matter volume and resting cerebral blood flow (CBF) as measured by pCASL generation software described below. As with the activation analyses, more specific age (years) and sex associations with activation will be assessed within each of the age groups. We will also examine the association of psychophysical data with regional brain connectivity metrics. To correct for multiple comparisons in brain imaging data we will use 3dClustSim (Cox, 1996; Cox & Hyde, 1997; Gold et al., 1998).To calculate the corrected *p* value of the brain signal in a respective ROI. This program uses the intrinsic volume and Monte Carlo simulations set at 10,000 iterations. A corrected voxel size of activation will be provided for each ROI to determine statistical significance. Data distributions will be evaluated and transformed as needed to meet the assumptions of the specific statistical methods and p‐values of 0.05 will be used for all tests.

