#### Sample size estimation

2.6.4

Case/control groups of the size proposed in this research (30 younger adults, 30 older adults) will provide 80% statistical power to detect a difference in outcomes of interest as small as half a standard deviation in the distributions of the observed values. This represents a large difference in terms of the expected control values. Given that this is a preliminary exploratory study, we want to focus on detecting larger effects. For example, assuming that we find that the younger group reports that mild pain is experienced on average at 35°C (*SD* 6°C) with a corresponding unpleasantness rating of mean 9.2 (*SD* 4.0), our group sizes can detect an increase in the temperature level for mild pain in the older group as small as 3°C and a difference in unpleasantness ratings as small as 2 scale points. The same logic will hold for the activation and functional connectivity age group analyses. Using data from previous ageing research (Cole et al., 2006, 2010) we can expect that our control participants may have activation values (as Z scores) with approximate *mean* = 3.81 and *SD* 0.46. Given our proposed sample sizes, a respective case activation mean value of ~4.04 would be statistically significant. Correlations between observed values (e.g., pain, age, depression, anxiety, and activation in an ROI) as small in absolute value as 0.34 will be statistically significant (*p* < .05).

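### The primary age-by-sex interaction cannot by itself confirm hypotheses that predict a signed age slope in women and a weaker one in men

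*Protocol article*

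**What the plan says.** Section 2.1 (Aims) gives two hypotheses under each of two aims. The age-by-sex part of each has the same shape. Age is positively related to thresholds (Aim 1, Hypothesis 1), negatively to unpleasantness (Aim 1, Hypothesis 2), and positively to activation in sensory and affective regions (Aim 2, Hypotheses 1 and 2). In every case the relation is stated for females and said to be weaker in males.

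Section 2.6 (Data analysis) enters age, sex and their product into a general linear model. It describes the hypotheses as differing patterns by sex and concludes: "therefore the interaction term will be the primary effect of interest in these analyses". It adds: "Main effects of ageing and sex will be tested; however, they will serve as covariates in the primary analyses". On error rates it says "All statistical significance tests will maintain Type I error rates (alpha values) of no more than 0.05", without stating sidedness.

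For Aim 1, section 2.6.1 also describes an overall age effect, and a further test: "This effect would be indicated by a statistically significant interaction of age level with" the self-reported sensory level. No sex term is mentioned there. Section 2.6.2 speaks of age and sex associations inside age groups, not of age slopes inside each sex.

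**The concern.** Each hypothesis makes two claims: the female age slope has a given sign, and it exceeds the male slope in that direction. The interaction coefficient estimates only the female slope minus the male slope. A significant value with the predicted sign is necessary for the hypothesis but not sufficient. It also arises when women show no age effect and men move against the prediction, or when both sexes move against it and men do so more.

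The Conclusion (section 4) draws implications for older compared with younger women if the hypotheses are borne out. Those implications need an age effect in women, which the named primary effect does not establish.

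**Working it through.** **Plan's own figure.** The article gives no power figure for the interaction. Section 2.6.4 refers to age groups ("30 younger adults, 30 older adults") and says that these "will provide 80% statistical power to detect a difference in outcomes of interest as small as half a standard deviation". That figure does not reproduce: 0.5/√(2/30) = 1.94, and Φ(1.94 − 1.96) is about 49% two-sided. This is a separate matter and nothing below depends on it.

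**Inputs from the article (section 2.3).** "we will enroll 60 subjects", stratified "to allot 5 males/5 females) to each of six age strata". That gives 5 × 6 = 30 per sex, with ages 30–89.

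**Assumptions.** One outcome with residual SD 1; slopes in residual SD per SD of age; two-sided 0.05; model age + sex + age × sex with 60 − 4 = 56 degrees of freedom. The article gives no slopes, so a difference of 0.6 is used for illustration. Signs are written for a positive prediction; reverse them for unpleasantness.

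**Interaction, by formula.**
- With age standardised, the age sum of squares is about 30 in each sex.
- SE of the slope difference = √(1/30 + 1/30) = 0.258.
- Difference/SE = 0.6/0.258 = 2.32; the critical t on 56 df is 2.00.
- Chance of significance in the predicted direction ≈ Φ(2.32 − 2.00) = Φ(0.32) ≈ 63%.

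Only the difference enters this calculation. The result is the same for female 0.6/male 0, female 0/male −0.6, and female −0.3/male −0.9.

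**Female slope, by formula.** SE = √(1/30) = 0.183.
- True female slope 0: about 2.5% significant in the predicted direction.
- True female slope −0.3: Φ(−0.3/0.183 − 2.00) = Φ(−3.64) ≈ 0.01%.

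**Simulation** (5 per sex per decade). The third column adds the requirement of a significant female slope of the predicted sign.

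| True slopes (female / male) | Hypothesis | Interaction, predicted sign | Both conditions |
|---|---|---|---|
| 0 / −0.6 | false | about 63% | 2.7% |
| −0.3 / −0.9 | false | about 63% | 0.01% |
| 0.6 / 0 | true | 62.9% | 61.7% |
| 0.9 / 0.3 | true | 62.4% | 62.4% |
| 0.4 / −0.2 | true if an opposite male slope counts as weaker | 62% | 47% |
| 0.3 / −0.3 | same | 62% | 33% |
| 0.2 / −0.4 | same | 61% | 17% |

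At a larger difference of 0.8 the contrast is sharper. The interaction is significant in the predicted direction in 86.2% of runs with female 0/male −0.8, against 2.7% under both conditions. With female 0.8/male 0 the figures are 86.1% and 86.0%.

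**Other tests in the plan.** None supplies the missing part. The age coefficient beside an interaction is a reference-sex slope or an average slope, depending on coding that is not stated. The age-by-sensory-level test has no sex term. The analyses inside age groups do not estimate a lifespan slope in women.

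**The case against.** The strongest defence is that probing an interaction is routine, that a condensed article may leave it to a fuller plan, and that this is an exploratory study whose fitted model already contains both sex-specific slopes. Nothing is lost irrecoverably, and the authors never say that a significant interaction alone proves a hypothesis. This limits the severity. It does not remove the point, because the article names a primary effect and ties it to signed hypotheses, and the two do not match.

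The main effects are also tested and could raise an alarm. If age were coded as the average slope, it would be significant against the prediction in about 62% of runs for female 0/male −0.6 and about 99% for female −0.3/male −0.9. That is a fair reminder that the interaction is not the whole analysis. But the coding is unstated, the term is called a covariate, and an average slope is not the female slope.

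A reader might go further and infer that the plan would count a reversed pattern, such as a steeper positive slope in men, as support. The documents do not bear that out. Section 2.1 states the direction of every age association, and section 2.2 says that findings will be read against a model with larger changes in females. A reversed interaction would mislead only someone who ignored its sign, so it is not used as evidence here.

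Finally, the simulation uses a single-outcome linear model. Aim 1 has three pain levels with robust variance estimation, and Aim 2 uses image maps with cluster correction. The percentages are therefore illustrative. That the interaction tests only a slope difference does not depend on the model used.

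**Conclusion.** The point holds for the named primary effect. Section 2.6 tests whether the age slopes differ by sex, while section 2.1 predicts a signed slope in women that is also stronger than in men. Even when the predicted sign is required, the test is as likely to be positive in the two false situations examined as when the hypothesis is true: about 63% at a slope difference of 0.6 with 30 per sex. The size rests on the assumed slopes, unit residual SD and two-sided 0.05. The mismatch itself needs none of these, and one-sided testing would not cure it. It is worth correcting before analysis, but it does not undermine the design.

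**What to change.** Add to section 2.6: an age-by-sex hypothesis is supported only if (1) the interaction is significant with the predicted sign and (2) the female age slope from the same model is significant in the predicted direction. Report both sex-specific slopes with confidence intervals whatever the result. Because both conditions must hold, combining them needs no extra alpha correction; multiplicity over pain levels and brain regions is a separate question. For Aim 2, say whether both conditions apply to a regional summary or to the same voxels.

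No new data are needed. In the scenarios run, the power cost is about one percentage point or less when the male slope is zero or in the predicted direction (62.9% to 61.7%, and none at 0.9/0.3). It is substantial, about 14 to 45 points, when the male slope is opposite in sign, because the female slope is then small and hard to demonstrate with 30 women. The authors should accept that cost openly, or else limit the claim to a sex difference in slopes.

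### Section 2.6.1 judges the Aim 1 hypotheses by an age-by-sensory-level interaction that omits sex, in conflict with the hypotheses and with the age-by-sex effect that section 2.6 makes primary

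*Protocol article*

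**What the plan says.** Section 2.1.1 of the protocol article gives each Aim 1 hypothesis two clauses. The first is that the age association (positive for threshold temperature, negative for unpleasantness) is present in females and weaker in males. The second is a female-male difference: lower thresholds and less unpleasantness in females.

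Section 2.6 lists age, sex and their interaction as model terms for the psychophysical and the imaging data. Because different age patterns are expected in the two sexes, it concludes that "the interaction term will be the primary effect of interest in these analyses".

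Section 2.6.1 then turns to Aim 1. It restates what is tested, for a given sensory threshold, as "temperatures are higher, and ratings of unpleasantness are lower with increasing age". It continues: "This effect would be indicated by a statistically significant interaction of age level with self‐reported sensory level on the dependent variables", and attaches the labels of Hypothesis 1 (temperature) and Hypothesis 2 (unpleasantness) to that sentence. Its fallback covers a significant age association "but no interaction effect will indicate an age effect on temperature and unpleasantness regardless of perceived pain". Sex is not mentioned anywhere in 2.6.1.

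**The concern.** Section 2.6.1 is where the reader learns how Aim 1 will be decided, and the term it names answers a different question from the one asked. Age-by-level asks whether the age slope differs between just noticeable pain (JNP), weak pain (WP) and moderate pain (MP). No hypothesis in 2.1.1 says that it does. The hypotheses ask whether the age slope differs between females and males.

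The term is also wrong for 2.6.1's own sex-free restatement. Higher temperatures with age at a given level is an age effect at each level, not a difference in age effects between levels.

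At stake is what Aim 1 can conclude. An analyst who follows 2.6.1 could report no support when the hypothesised sex difference is present, or support when it is absent. With 2.6 and 2.6.1 both in force, the criterion can also be chosen after the results are seen.

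**Working it through.** **The plan's own figure.** The only power statement (section 2.6.4) is 80% for half a standard deviation between 30 younger and 30 older adults. It concerns an age-group difference, not either interaction. It also does not reproduce: 0.5 / √(2/30) = 1.94, and 1.94 − 1.96 ≈ −0.02, which gives about 49% two-sided. That is a separate matter and nothing below depends on it.

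**Algebra, with no assumed figures.** Let β(j,s) be the age slope at level j (JNP, WP, MP) in sex s.

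- First clause of Hypotheses 1 and 2: β(j,F) differs from β(j,M). This is age-by-sex.
- Restatement in 2.6.1: the age slope at each level is non-zero (positive for temperature, negative for unpleasantness). This is an age effect.
- Criterion in 2.6.1: the age slope is not the same at JNP, WP and MP. This is age-by-level.

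If β(j,F) = b and β(j,M) = c at every level, every age-by-level contrast is b − b = 0 or c − c = 0, whatever b and c are. The first clause and the restatement can both be true while the criterion is exactly null.

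**Size.** Inputs from the document: 60 participants, 5 per sex in each of six decades from 30 to 89; three levels; SD 6 °C (section 2.6.4); alpha 0.05. Assumptions not in the document: two-sided tests, within-subject correlation ρ of 0.5, 0.7 or 0.9, and age slopes in °C per 30 years that are equal across levels. There were 4,000 simulated studies per scenario. Ranges run over the three values of ρ.

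| Slope in females / males | Age-by-level significant | Age-by-sex significant | Age effect significant |
|---|---|---|---|
| 3 / 0 | 5.3–5.5% | 20–27% | 20–27% |
| 6 / 2 | 4.6–5.1% | 33–42% | 85–95% |
| 6 / 0 | 4.7–5.5% | 63–77% | 61–78% |
| 9 / 0 | 4.6–5.0% | 93–98% | 93–98% |
| +3 / −3 (ρ = 0.7 only) | 5.2% | 68.5% | 5.0% |

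**Hand check of the age-by-sex column at ρ = 0.7.** The variance of a participant's mean over three levels is 36 × (0.7 + 0.3/3) = 28.8. Age in units of 30 years, spread evenly over 60 years, has variance 2²/12 = 1/3. The standard error of the slope difference is √(28.8 / (60 × 1/3 × 1/4)) = √(28.8/5) = 2.4. For a difference of 6, 6/2.4 − 1.96 = 0.54, so power is about 70.5%; the simulation gave 70.1%. For a difference of 4, 4/2.4 − 1.96 = −0.29, so about 38.5%; the simulation gave 37.8%.

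**A second simulation** (5,000 studies, total SD 1, ρ = 0.6) used 0.40 SD per decade in females and 0 in males, which is 0.40 × 3 × 6 = 7.2 °C per 30 years. Age-by-level was significant in 4.6%, age-by-sex in 85.9% and age in 87.2%. With a common slope of 0.25 SD per decade in both sexes, the figures were 5.2%, 5.3% and 97.2%.

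**The reverse error.** With no sex difference and slopes of 0, 3 and 6 °C per 30 years at the three levels (ρ = 0.7), age-by-level was significant in about 100% of studies and age-by-sex in 5.2%.

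**The case against.** The strongest reply is that the right test is already in the plan. Section 2.6 applies age-by-sex to the psychophysical data by name, and 2.6.1 sits beneath it and withdraws nothing. This stands. A reader might infer that the study has no test of its hypotheses and that a true effect would simply be missed. The document does not support that: the loss arises only if 2.6.1 is taken as the criterion in place of 2.6.

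A reader might also infer that two primary tests are named. They are not: only 2.6 uses the word primary.

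Nor does the text say that an age-by-level result would be reported as confirming a sex difference. The effect meant in 2.6.1 is the sex-free age statement just before it, and the hypothesis labels may only index the two outcomes. On that reading 2.6.1 covers the age component and 2.6 the sex comparison. The labels are ambiguous enough that the misreading is possible, but it remains a possibility.

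The fallback also counts. Where both sexes share the same slope at all levels, the age effect is found (97.2% above), so nothing is lost there. Where only females have a slope, the fallback reports an average age effect. It never shows the sex difference, and with opposite slopes it shows nothing (5.0%).

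Finally, the 5% depends on slopes being parallel across levels, which the document does not state. If the slopes vary by level, age-by-level has power, but a significant result still says nothing about sex. The exploratory label and the condensed format do not dispose of the point, because the article states a criterion and that criterion does not fit.

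**Conclusion.** The point holds as an internal conflict. Section 2.6.1 states a criterion for Aim 1 that omits sex, disagrees with 2.1.1 and 2.6, and does not test its own restated hypothesis. The second clause of each hypothesis, the female-male difference, is not addressed in 2.6.1 either.

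If 2.6.1 is followed and the slopes are parallel across levels, age-by-level supports the hypothesised sex difference at about the alpha level, however large that difference is. This figure needs no assumption about slope size or correlation. The power of the age-by-sex test in 2.6 does depend on such assumptions: about 20% to 98% for slope differences of 3 to 9 °C per 30 years. These figures illustrate the contrast between the two criteria and do not forecast this study's power.

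**What to change.** Reword 2.6.1 so that it agrees with 2.6. For temperature and for unpleasantness, use the repeated-measures model already planned, with sensory level, age, sex and age-by-sex:

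- The age-by-sex term is the stated test of the first clause of Hypotheses 1 and 2, reported with the age slope in each sex. Say whether it is taken over all three levels or at a named level.
- The sex contrast from the same model tests the second clause, with age centred so that the contrast refers to a stated age.
- The age effect at a given level is read from the age term.
- Age-by-level and age-by-sex-by-level are secondary tests of whether the pattern varies with pain level.

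The cost is a few sentences. Participants, measurements and model family are unchanged. The rewording does not raise the power of the age-by-sex test; it only settles which test decides Aim 1.
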